## Methodology

### Study design and setting

A before-after designed intervention study will be conducted in two randomly selected secondary schools in a semi-urban area of Dhaka, capital of Bangladesh. One school will be selected randomly as intervention school and the other one as control school. Possibility of diffusion of intervention contents among students from one school to another will be minimized by selecting the schools at a reasonable distance.

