### Participant recruitment and data collection

The study will follow a fixed study design (Additional file 1). Sample size is determined based on a previous study where a mean difference of BMI was found 1.48 between intervention and non-intervention adolescent groups after 3-months of motivational interview [23]. Expecting a similar difference, calculated sample size is 274 in each group considering effect size (E) = 1.48; standard deviation (S) = 5.98; standardized effect size (E/S) = .25; significance level, α (two-sided) = 0.05; β = 1- power = 0.2, non-response rate = 5%]. A complete list of grade-ten students will be prepared after collecting their class roll and batch number from the administrative offices of the selected schools. All the students of grade-ten will be invited to participate in the study through announcement and personal contact prior to the date of data collection.

At first, a baseline survey will be conducted among the grade ten students of both schools by a pre-tested questionnaire to attain their current status of knowledge, attitude and practices related to NCDs. Then, students from the intervention school who reported at least two NCDs risk behaviors will be invited to participate in a health education session through phone call to their parents. Selected students who will present at the day of intervention will be considered having implied consent from their parents and will be enrolled in the intervention group up to the attainment of the required sample size. Enrolled students will be given intervention through health education session. Students with any kind of physical disability or limited movement will be excluded from the study. Students from the control group will receive a one-hour session on carrier guidance. Students will be kept blind about the intervention they received. After 3 months of the baseline survey, a post-intervention survey will be conducted among the participants from both intervention and control group using the same questionnaire.

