### The intervention

Potential candidates for intervention will be divided into several groups based on their roll numbers. Each group will contain no more than 25 students. Then the intervention will be delivered to each group through health promotion sessions.

The intervention has been developed with the help of a psychologist, a nutritionist, a child health specialist and some public health specialists having experiences to work with adolescent health. Content of the intervention will be further improved and customized after baseline survey addressing the barriers to healthy behaviors among the target population.

The conceptual framework of the expected change through this intervention is as follows:

Intervention will be given on the following issues:

Issue 1: DietUnderstanding that there is an effect of every food we eat on our body and health besides alleviating our appetiteDemonstrating all the foods we eat every day and grouping them according to their nutritional valuesUnderstanding the metabolism and function of different food groups- carbohydrate, protein, fruits and vegetables, fries and fast food, soft and energy drinksUnderstanding and identifying healthy and unhealthy food options depending on its functionUnderstanding and identifying the link between unhealthy food options and NCDsRaising curiosity on what should be the food options to prevent NCDs

Issue 2: Physical activityDemonstrating the concept of physical activity and sedentary behaviorUnderstanding and identifying the link between physical inactivity and NCDsUnderstanding the benefits of three types of exercise (i.e., aerobic, strength building and stretching)Raising curiosity on how much and what type of physical activity should an adolescent do to prevent NCDs

Issue 3: ObesityDemonstrating the concept of normal weight and obesityEnabling to calculate one’s Body Mass Index (BMI) statusUnderstanding and identifying the potential causes of obesityUnderstanding the health consequence of childhood obesityRaising curiosity on what should be the ideal weight to stay fit and how to achieve it

Issue 4: SmokingUnderstanding the concept and the effect of active and passive smokingUnderstanding the relation of smoking with NCDsIdentifying the common reasons to start smoking at adolescent ageRaising curiosity on how to avoid starting smoking or how to quit smoking or how to reduce passive smoking

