Once the students are motivated enough to show their interest in healthy behavior, the process of negotiating change and strengthening commitment will be started by providing information. The information will be delivered in a structured way based on the principles of Bandura’s Social Cognitive Theory (SCT) [12]. The objective is to improve psychological determinants of behavior through observational learning. This intervention will emphasize supporting self-efficacy that is the belief in performance which brings the desire change [13]. As for example, if self-efficacy of a student about healthy diet is high, it means he believes that he can manage healthy eating at any situation. In this intervention, focus will be given on improving this self-efficacy through sharing experience, modeling and through verbal persuasion using some trend words, like “you are Bangladesh, you can do it”. In addition, education about NCDs and its risk factors will be given in such a way that allows them to reflect, letting them develop, and evaluate their own outcome expectancy which is, another behavior changing component of Bandura’s theory [18].

This intervention is not aimed to bring any environmental change. Yet, this intervention will demonstrate choices and make them skilled, thus empower them to pick the most suitable choice for themselves. As for example, they will be taught with a range of free hand exercises by role modeling and by making some role models among themselves. Now as they are mastered on several exercises, they can do any of them at their convenience, to acquire the daily physical activity recommendation. Leaflets on healthy diet, physical activity and anti-tobacco message will be provided to take home, which is expected to improve the social support to some extent. These will eventually improve their self-efficacy and self-regulatory capacity and thus influence health behavior.

An intervention is judged by its cost-effectiveness when referring for mass population. Meta-analysis on this issue found that group intervention is the least expensive yet most cost-effective interventional way among the adolescents [37]. This proposed intervention is designed for group and therefore, is more realistic in the low socio-economic context like Bangladesh to deliver the intervention to utilize the limited resources best. Thus, upon its effectiveness being proven, this intervention can be advocated to policies.

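### The 80% power for 274 students per group holds only if between-school variance is zero, which a design with one school per arm cannot check

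*Protocol article*

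**What the plan says.** In the Protocol article, the section Study design and setting fixes the allocation: "One school will be selected randomly as intervention school and the other one as control school". The study has two schools in all.

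The section Participant recruitment and data collection gives the sample size. It starts from an earlier study in which "a mean difference of BMI was found 1.48 between intervention and non-intervention adolescent groups after 3-months of motivational interview", expects a similar difference, and concludes: "calculated sample size is 274 in each group considering effect size (E) = 1.48; standard deviation (S) = 5.98". The other inputs are "standardized effect size (E/S) = .25", "significance level, α (two-sided) = 0.05", "β = 1- power = 0.2" and 5% non-response. No ICC, design effect or number of clusters enters the calculation.

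The Statistical analysis plan section names paired t-tests and McNemar tests for the before-after data. It also announces an intervention-control comparison of knowledge, attitude and practice, without naming a test for it. Under The intervention, delivery is in sessions: "Each group will contain no more than 25 students". The article does not mention clustering, or the limit set by one school per arm.

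**The concern.** The quantity that was powered is a difference between groups, and each group is one school. Whatever makes the two schools differ at endline, apart from the intervention, adds to that difference in full: intake, teaching, surroundings, or events during the three months. Enrolling more students in the same two schools does not average it out. With one school per arm there are no degrees of freedom for variation between schools within an arm, so the data cannot show how large this component is.

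Two things are at stake. The stated power is presented as a property of the design when it is conditional on an assumption that the article does not state. And if the arms are compared by a test that treats students as independent, a difference between two schools may be reported as an intervention effect at a nominal 5% level that does not apply.

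**Working it through.** **Inputs from the article:** E = 1.48, S = 5.98, two-sided alpha 0.05, power 0.80, non-response 5%, one school per arm. **Assumed, because the article gives no value:** ICC between 0.001 and 0.05.

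**1. Reproduce the stated figure.** Standardized effect d = 1.48/5.98 = 0.2475. For independent students:

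n per group = 2 × (1.960 + 0.842)² / 0.2475² = 256.3, so 257.

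With 5% non-response, 257/0.95 = 270.5, so 271. The stated 274 is about 1% above this. With d rounded to 0.25 the result is 252, then 266, which is within 3% of 274. There is no room in the figure for a design effect. The arithmetic is sound for independent students: power is 82.6% with 274 analysed per group and 80.6% with 260 (274 × 0.95 = 260.3).

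**2. Put the school into the variance.** With one school of m students per arm, the variance of the difference in means is (2S²/m) × DE, with DE = 1 + (m − 1) × ICC. For m = 260:

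- effective n = 260/DE;
- power = Φ(d√(effective n/2) − 1.96) plus the small opposite tail, treating the school variance as known, which is optimistic;
- type I error of a test that ignores the school = 2 × [1 − Φ(1.96/√DE)].

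Worked example, ICC = 0.01: DE = 1 + 259 × 0.01 = 3.59; effective n = 72.4; 0.2475 × √36.2 = 1.489; power = Φ(−0.471) = 32%. Type I error = 2 × [1 − Φ(1.034)] = 30%.

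| Assumed ICC | DE | Effective n per arm | Power, endline contrast | Type I error, school ignored |
|---|---|---|---|---|
| 0 | 1.00 | 260 | 81% | 5% |
| 0.001 | 1.26 | 206.5 | 71% | 8% |
| 0.005 | 2.30 | 113.3 | 46% | 20% |
| 0.01 | 3.59 | 72.4 | 32% | 30% |
| 0.02 | 6.18 | 42.1 | 21% | 43% |
| 0.05 | 13.95 | 18.6 | 12% | 60% |

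**3. Ceiling with two schools.** As m grows without limit, the standard error tends to S√(2 × ICC). At ICC 0.01, power tends to Φ(0.2475/0.1414 − 1.96) = Φ(−0.21) = 42%. Power of 80% needs ICC ≤ d²/[2 × (1.960 + 0.842)²] = 0.0613/15.70 = 0.0039. Above that value no number of students suffices.

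**4. How far the table depends on the type of contrast.** The stated SD is used as cross-sectional, so the table describes a comparison at endline. For change scores, with pre-post correlation r, the standardized effect becomes d/√[2(1 − r)], which equals d only at r = 0.5. The article gives no r. Assuming r = 0.8, it is 0.2475/√0.4 = 0.391. With 260 independent students per school, power would then be about 99%. At a school-by-time ICC of 0.01 it is Φ(0.391 × √36.2 − 1.96) = Φ(0.39) = 65%. The type I column depends on DE alone and is the same for a given ICC of the change.

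**The case against.** **Before-after analysis.** The study is described as a before-after study to be reported under guidance for non-randomized designs, and its named efficacy tests are paired. A contrast of changes, or one adjusted for baseline, could have clearly higher power than the table shows, as step 4 illustrates. This stands, and it is why the table must be labelled endline-only. It does not remove the point. The sample size is for a difference between groups. A paired test within one school cannot separate the intervention from that school's own change over three months. A contrast of changes has its own school-by-time component, which two schools cannot identify either.

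**Size of the distortion.** The ICC range has no source in the article, and at 0.001 the loss is modest (71% power, 8% type I error). A reader might infer that the trial's p-values are shown to be far too small. The documents do not establish that; the size is an assumption. What does not depend on the ICC is that the school variance cannot be estimated.

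**Planned tests.** A reader might infer that every planned analysis ignores clustering. The article names no test for the intervention-control comparison of outcomes, and a separate analysis plan is not shown. The point rests on the stated power basis, not on missing analysis detail.

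**Delivery sessions.** A reader might add that sessions of up to 25 inflate the error of the paired tests. That requires effects that vary by session, or sessions that coincide with existing classes. The article states neither: groups are formed by roll number, and facilitators follow written dialogues with their lectures checked for similarity.

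**Policy wording.** The Discussion says that "upon its effectiveness being proven, this intervention can be advocated to policies". A reader might take this as a promise that this study will prove effectiveness. It is conditional, and the section closes more modestly, citing limited time and money.

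**Conclusion.** The concern holds for the power statement. The figure of 274 per group with 80% power follows from independent students; the design has one school per arm. The 80% is therefore conditional on zero between-school variance, a condition that is unstated and that the trial cannot test. Intervention and school are confounded at any ICC.

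The sizes are illustrative. For an endline contrast with SD 5.98 and 260 per school, power runs from about 71% down to 12%, and unadjusted type I error from about 8% up to 60%, over assumed ICCs from 0.001 to 0.05. Power of 80% is out of reach above an ICC of about 0.004. Treating the school variance as known favours the design, since two schools provide no estimate of it. A change-score or baseline-adjusted contrast may do better on power by an amount that depends on the pre-post correlation, with the same unidentifiable component.

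**What to change.** In Participant recruitment and data collection, state that 274 per group gives 80% power only if between-school variance is zero, and add a table of power over an assumed ICC range such as 0.001 to 0.05, labelled as an endline contrast with the stated SD. Report the intervention-control contrast with intervals shown across that range. State the conclusion as a two-school, hypothesis-generating comparison in which the intervention cannot be separated from the school.

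Two additions are optional. Accounting for delivery sessions (274/25 = 10.96, so at least 11) can serve as a sensitivity analysis, but it leaves the school confounding untouched and 11 clusters are few for robust standard errors. The policy sentence in the Discussion could be softened.

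The cost is wording and a modest addition to the analysis, with no extra enrolment. The downside is that the stated power and the strength of the claim become less favourable. Keeping a confirmatory claim would take several schools per arm and an analysis that accounts for school, which is a different study.

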## Objectives

### General objective

To design and investigate the efficacy of a health education intervention to reduce NCD related behavioral risk factors among adolescents in institutional settings of Bangladesh.

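### The 80% power and 5% alpha claimed for 274 students per group hold only if schools do not differ, which one school per arm cannot show

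*Protocol article*

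**What the plan says.** Under Study design and setting, the protocol article describes a before-after intervention study in two schools: "One school will be selected randomly as intervention school and the other one as control school". Each arm is therefore a single school.

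Under Participant recruitment and data collection, the "calculated sample size is 274 in each group considering effect size (E) = 1.48", with "standard deviation (S) = 5.98", "standardized effect size (E/S) = .25", "significance level, α (two-sided) = 0.05" and "β = 1- power = 0.2, non-response rate = 5"%. The 1.48 is a difference in BMI between intervention and non-intervention adolescents at 3 months, taken from a cited study. No ICC, design effect or number of clusters is given.

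Under Statistical analysis plan, efficacy is to be judged from before-after data by paired t-tests and McNemar tests. Intervention and control are also to be compared on knowledge, attitude and practices, before and after. No allowance for school is stated.

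The general objective is "To design and investigate the efficacy of a health education intervention", and the Discussion looks ahead: "Thus, upon its effectiveness being proven, this intervention can be advocated to policies". The section on reporting commits to TREND, the checklist for non-randomized evaluations. The article does not say that the effect of the school cannot be separated from that of the intervention.

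**The concern.** The sample size treats each student as a separately allocated unit, but the unit allocated is the school. Students in one school share teachers, surroundings and events, and that shared component does not average out as more of them are recruited. With one school per arm, it is also indistinguishable from the intervention.

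At stake is the only power statement in the article. A reader would take 80% and 5% as properties of the study. If schools vary even slightly, the true power of the planned contrast is lower and its true false-positive rate higher. A statistically significant difference between two schools could then be carried into the policy step that the Discussion foresees.

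**Working it through.** **Inputs from the article:** E = 1.48 kg/m², S = 5.98, two-sided alpha 0.05, power 0.80, non-response 5%, 274 per group, one school per arm.

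**Assumed:** ICC between 0.001 and 0.02, because the documents give none.

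**1. Reproducing 274.**

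n = 2(1.96 + 0.8416)² / (1.48/5.98)² = 256.3, so 257 per group. Allowing for 5% non-response, 257/0.95 = 270.5, so 271. This is within about 1% of 274. The stated figure is the formula for two independent samples of individuals, with a design effect of 1.

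**2. Power with independent students.**

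Completers: 274 × 0.95 ≈ 260 per school. SE = 5.98 × √(2/260) = 0.524 and 1.48/0.524 = 2.82, giving power Φ(2.82 − 1.96) ≈ 81%. The claim is met if the ICC is zero.

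**3. Adding a school component (post-intervention BMI contrast).**

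- Design effect: DE = 1 + 259 × ICC
- SE = 0.524 × √DE
- Power if the ICC were known: Φ(1.48/SE − 1.96) + Φ(−1.48/SE − 1.96)
- False-positive rate of the unadjusted student-level test: 2[1 − Φ(1.96/√DE)]

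| Assumed ICC | DE | SE | Power, ICC known | Unadjusted false-positive rate |
|---|---|---|---|---|
| 0 | 1.00 | 0.52 | 81% | 5% |
| 0.001 | 1.26 | 0.59 | 71% | 8% |
| 0.005 | 2.30 | 0.79 | 46% | 20% |
| 0.01 | 3.59 | 0.99 | 32% | 30% |
| 0.02 | 6.18 | 1.30 | 21% | 43% |

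At ICC 0.01 the chance difference between two school BMI means has SD 5.98 × √(2 × 0.01) = 0.85 kg/m², or 57% of 1.48.

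**4. Can more students repair it?**

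With unlimited students the variance of the contrast falls only to 2 × ICC × S². For 80% power the ICC must then not exceed (1.48/5.98)² / [2(1.96 + 0.8416)²] ≈ 0.0039. Above that, no number of students in these two schools reaches 80%.

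**5. Can the data supply the ICC?**

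Two schools in two arms leave 2 − 2 = 0 degrees of freedom for between-school variance. It can be assumed but not estimated.

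**6. What a comparison of changes would do.**

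Take ICC 0.01 and assume the same pre-post correlation ρ for students and schools. The SD of change is 5.98 × √[2(1 − ρ)]. With DE 3.59 as above, power is about 32%, 49%, 65% and 91% at ρ = 0.5, 0.7, 0.8 and 0.9. The false-positive rate of an unadjusted test stays near 30%, because DE is unchanged.

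**The case against.** The strongest reply is that this is a before-after study. Both schools are measured at baseline, so a stable difference between them is visible and cancels when changes are compared. This stands. A reader might infer that every difference between the schools passes in full into every contrast; the documents do not support that. Step 6 shows that power for a comparison of changes can be well above 32% if BMI is strongly correlated over time. What does not cancel is a change over the 3 months that is specific to one school.

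Nor do the paired tests escape the problem. Taken alone they do not use the control school, so they cannot separate the intervention from 3 months of ordinary change. The article does not explicitly specify a comparison of changes between the schools.

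A second reply is that the power table describes a contrast the analysis section does not name, since the between-group comparison listed there covers knowledge, attitude and practices. This also stands. The table applies to the BMI difference on which the article bases its sample size, and to nothing else.

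A third reply is that the before-after label, the TREND commitment and the acknowledged limits of time and funding already concede a modest design, and that the policy sentence is conditional. That is fair as to tone, but none of it discloses that school and intervention are confounded or qualifies the stated power.

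Deferring to a separate analysis plan does not help either, because no analysis can recover a variance with 0 degrees of freedom.

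**Conclusion.** The concern holds in a limited form. The power and alpha are stated without a condition they need: no between-school variation, which this design cannot check. For the post-intervention BMI contrast, power falls to between about 71% and 21%, and the unadjusted false-positive rate rises to between about 8% and 43%, over assumed ICCs of 0.001 to 0.02. These rest on 260 completers per school and a normal approximation. The ICCs are illustrations, not estimates for these schools.

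Two stronger readings are tempting and not supported. One is that 274 is miscalculated: it reproduces closely, and the fault lies in applying an individual-level formula to a two-school allocation. The other is that nothing can be learned about the intervention. A descriptive or pilot conclusion remains possible. What is missing is a basis for causal inference without assuming that neither school changed for reasons of its own.

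**What to change.** 1. **Participant recruitment and data collection.** State that 80% power and 5% alpha assume zero between-school variation and that one school per arm cannot verify this. Give the power and false-positive figures above, labelled as illustrations under assumed ICCs for the post-intervention BMI contrast only.
2. **Statistical analysis plan.** Base the between-school comparison on change from baseline, or adjust for baseline. Add a sensitivity table that widens its interval over an assumed range of school-level variation in change. With τ the assumed school-level SD of change, the squared standard error becomes the student-level one plus 2τ². The table shows how large τ must be before the conclusion is lost; it does not estimate τ.
3. **General objective and Discussion.** Limit the conclusion to a controlled before-after comparison of two schools. Make no causal efficacy claim unless the assumption of no school-specific change is stated with it.

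The cost is wording, one extra table and a less favourable power statement. No more students are needed.

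If the schools are not yet fixed, the same students could be drawn from several schools per arm. Registration was retrospective, so the schools may already be fixed. This option makes between-school variation estimable but does not by itself restore 80% power. With 5 schools per arm (52 completers each) and an assumed ICC of 0.01, DE = 1 + 51 × 0.01 = 1.51 and SE = 0.524 × √1.51 = 0.644. Power is then about 63% by normal approximation, and only about half with a t-test on 8 degrees of freedom.

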**Methods:**

A before-after designed intervention study will be conducted in two randomly selected secondary schools- one will be selected randomly as intervention school and the another as control school. A baseline survey will be conducted among the students of both schools by a pre-tested questionnaire to attain their current status of knowledge, attitude and practices related to NCDs. Afterward, students will be enrolled in the intervention group who will meet the eligibility criteria from the intervention school. The intervention will be given through a health promotion session to a group of students, not more than 25 at a time, by trained facilitators. A post-intervention end line survey will be conducted among all the participants from both schools using the same questionnaire 3 months after the baseline survey.

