### Statistical analysis plan

Descriptive analysis: Socio-demographic data of the participants e.g. gender, parental occupation, parental education status, family history of NCDs, family living standard will be obtained for both intervention and control school. All categorical variables will be summarized in frequency and percentages and continuous variables in mean and standard deviation. To estimate the association of these characteristics of intervention and control group, t-tests and chi-square tests will be done.

Inferential analysis: To estimate the efficacy of the intervention, before-after data will be analyzed and paired t-test and McNemar’s chi-square tests will be done in this regard. Also, comparison will be done between the intervention and control group for pre and post-intervention status of knowledge, attitude and practices.

Association analysis: Binary regression analysis will be done to estimate the association between socio-demographic variables with changes in the outcome variables- knowledge, attitude, and practice for both groups. Also, to estimate the association of knowledge score and attitude with the change in self-reported practices, regression analysis will be done.

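### The at-least-two-risk-behaviours entry rule is stated for the intervention school only, so before-after and change analyses of the practice outcomes can show benefit from regression to the mean alone.

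*Protocol article*

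**What the plan says.** All references are to the protocol article.

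- **Baseline (Participant recruitment and data collection).** "a baseline survey will be conducted among the grade ten students of both schools by a pre-tested questionnaire", so both schools supply the information needed to apply a risk-behaviour criterion.
- **Entry to the intervention group.** From that survey, "students from the intervention school who reported at least two NCDs risk behaviors will be invited to participate in a health education session". Those who attend are enrolled until the required number is reached. The Abstract (Methods) ties eligibility to the same school: "students will be enrolled in the intervention group who will meet the eligibility criteria from the intervention school".
- **Entry to the control group.** No risk-behaviour threshold is stated. The section says "Students from the control group will receive a one-hour session on carrier guidance", which concerns what controls receive and not who they are. The one criterion worded for the whole study is "Students with any kind of physical disability or limited movement will be excluded from the study".
- **Follow-up.** Three months after baseline, "a post-intervention survey will be conducted among the participants from both intervention and control group using the same questionnaire".
- **Analysis (Statistical analysis plan).** "To estimate the efficacy of the intervention, before-after data will be analyzed and paired t-test" and McNemar's test are named. In addition, "comparison will be done between the intervention and control group for pre and post-intervention status of knowledge, attitude and practices".

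**The concern.** Students enter the intervention group because their baseline report of the outcome was high. A self-administered questionnaire on diet, activity, smoking and alcohol has reporting error, and behaviour also varies over time. Some students pass the threshold by chance, so on average the selected group reports fewer risk behaviours on the second occasion whatever it was taught.

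A control group selected in the same way would fall by the same amount, and the fall would cancel in the between-group difference. An unselected control group has no expected fall, so subtracting its change removes nothing. The within-arm tests carry the artefact in full.

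Reducing behavioural risk factors is the general objective, and the Discussion proposes to advocate the intervention to policy if it proves effective. A false positive on the practice outcomes would therefore have consequences.

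**Working it through.** **The plan's own figure.** With E = 1.48, S = 5.98, two-sided alpha 0.05 and power 0.80, n = 2 × (1.96 + 0.8416)² × (5.98/1.48)² = 256.3, so 257. Allowing 5% non-response, 257/0.95 = 270.5, so 271, against the stated 274. The figure reproduces closely and does not bear on this point. It gives the number analysed used below: 274 × 0.95 = 260 per group.

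**Assumed inputs (not in the article).** Four independent yes/no risk behaviours (diet, inactivity, smoking, alcohol or substances) with assumed prevalences; test-retest agreement kappa k of 0.5 to 0.9; identical schools, no time trend and no intervention effect. At retest each behaviour keeps its baseline value with probability k and is otherwise redrawn at its prevalence. The intervention group is selected on a baseline count S of at least 2; controls are unselected.

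**Formula.** Expected spurious fall in the selected group = (1 − k) × (E[S | S ≥ 2] − E[S]). Expected change in unselected controls = 0.

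**Worked case, prevalences 60/60/30/10%, k = 0.6.**
1. P(S = 0) = 0.4 × 0.4 × 0.7 × 0.9 = 0.1008. P(S = 1) = 0.3568. P(S ≥ 2) = 1 − 0.1008 − 0.3568 = 0.5424, so 54% qualify.
2. E[S] = 1.60. E[S | S ≥ 2] = (1.60 − 0.3568)/0.5424 = 2.292.
3. Spurious fall = 0.4 × (2.292 − 1.60) = 0.277 behaviours.
4. The SD of change is 0.739 (selected) and 0.790 (unselected). SE of the difference = √((0.739² + 0.790²)/260) = 0.067, so the expected z is 0.277/0.067 = 4.1. The test of change falsely favours the intervention in about 98% of trials.
5. By behaviour, the falls are about 9, 9, 7 and 2.5 percentage points. McNemar's test in the intervention arm is falsely significant in about 94%, 94%, 71% and 26% of trials (nominal 5%).
6. End-line status: 2.292 − 0.277 = 2.02 behaviours in the selected group against 1.60 in controls. A comparison of end-line status alone makes the intervention look harmful.

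**Range.** False rejection in the intervention's favour, nominal 2.5%, for k = 0.5 / 0.7 / 0.9:

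| Prevalences (%) | Share qualifying | Spurious fall in count | Paired test | Between-group test of change |
|---|---|---|---|---|
| 60/60/30/10 | 54% | 0.35 / 0.21 / 0.07 | 100 / 99.9 / 81% | 99.7 / 94 / 52% |
| 90/70/40/5 | 78% | 0.16 / 0.10 / 0.03 | 96 / 80 / 35% | 71 / 49 / 19% |
| 95/80/50/5 | 88% | 0.09 / 0.05 / 0.02 | 60 / 39 / 16% | 32 / 21 / 10% |
| 95/90/50/5 | 93% | 0.06 / 0.03 / 0.01 | 30 / 19 / 9% | 16 / 11 / 6% |
| 98/98/50/5 | 98% | 0.015 / 0.009 / 0.003 | 6 / 5 / 4% | 5 / 4 / 3% |

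**Check with a continuous score.** If a share q qualifies above cut-point c on a normal score with reliability r, the spurious change is (1 − r) × φ(c)/q SD. At r = 0.7 this gives 0.35, 0.24, 0.15 and 0.06 SD for q = 30, 50, 70 and 90%. For scale only, the planned standardised effect, which is for BMI, is 0.25.

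**The case against.** - **Silence about controls is not proof that they are unfiltered.** This stands as a limit on wording. The article gives no control-group entry rule and refers to a fixed design in an additional file that is not shown. A reader might infer that controls are certainly unselected; the text supports only that no such criterion is stated for them. It is not merely detail left to a fuller document, because the article does state the rule and both times attaches it to the intervention school.
- **Not every planned comparison favours the intervention.** This also stands. It is tempting to say that both the before-after and the between-group analyses are biased towards benefit. The between-group comparison is described as one of pre and post status, and on end-line status alone the bias runs against the intervention. Only within-arm and change analyses lean in its favour.
- **Selection is on practices only.** Correct. Knowledge, attitude and BMI, on which the sample size rests, are affected only as far as they correlate with the selection error.
- **The definitions are broad, so nearly everyone may qualify.** Under Practice, fewer than five servings of fruit and fewer than five of vegetables a day already make a dietary risk, and frequent passive smoke exposure counts as smoking risk. High eligibility is plausible, and at 98% the distortion nearly vanishes. The article gives no eligibility rate, so the high false-positive figures cannot be presented as what this trial will show.
- **A large bias and a cheap remedy do not go together.** Partly right: low eligibility makes the bias large and also makes the matched control group small. The cost is stated under the fix.

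**Conclusion.** The concern holds for within-arm before-after tests and for any comparison of change on the self-reported practice outcomes. As written, the plan selects one arm on the outcome, re-measures it with the same instrument, and estimates efficacy with tests that cannot separate regression to the mean from benefit. An unselected control school could not correct this.

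The mechanism and its direction follow from the text. The size does not: it rests on assumed prevalences, independence between behaviours and kappa of 0.5 to 0.9. Across those assumptions it runs from nearly certain false positives when about half of students qualify to nearly nominal error when about 98% do.

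**What to change.** 1. **Recruitment.** State that the control analysis group is defined by the same rule as the intervention group: at least two risk behaviours at baseline and the same disability exclusion, taken from the control-school survey already planned.
2. **Analysis.** Make the efficacy estimate the between-group comparison in these matched groups, adjusted for the baseline value of the outcome and the baseline number of risk behaviours (or the difference in change). With identical schools both arms then regress equally and the expected spurious difference is zero. Keep the within-arm paired t and McNemar tests as descriptive only; they stay biased even when the rule is applied to both schools.
3. **Reporting.** Give the share of students in each school who meet the rule, since it determines how much the selection matters.

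**Cost.** Two sentences and no new measurements. Control students with fewer than two risks leave the main comparison. If 98% qualify, the loss is about 2%. If 54% qualify, it is about 46%, and 274 eligible controls would need about 274/0.5424 = 505 students surveyed; the article gives no grade-ten enrolment to judge this against. In that case all controls can be kept in a secondary baseline-adjusted analysis, with the caution that controls below the threshold have no counterparts in the intervention group and contribute only through the model.

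None of this addresses the separate problem of one school per arm.
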